| 5.Basic Study Design (Briefly describe your study):  Patients will be asked to run across a force platform (which measures ground reaction forces) while high speed cameras record body segment trajectories through space. Together, these data will allow us to noninvasively calculate internal forces at the knee joint. Each patient will be asked to perform trials with a neutral and experimental shoe conditions so that we can determine whether the experimental footwear reduces knee joint loading for PFPS patients. Then, each subject will receive either the neutral or an experimental shoe (this will be randomized and blinded for the patients) to take home for six weeks. The subjects will be asked to continue their training protocol and run on a regular basis with the shoe provided while knee pain levels and running mileage are subjectively monitored. At the end of the study, we will be able to determine if a decrease in knee joint loading is correlated with a decrease in knee pain. |

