| 6.Methods:  a) Subject numbers: How many local subjects? 30 How many total subjects? 30  *b) Major Inclusion/Exclusion Criteria:*  All patients must meet the following pre-established inclusion criteria (Lun et al., 2005; Stefanyshyn et al., 2006). These will be assessed by a sports medicine physician prior to beginning testing.  **History:** (1) Nontraumatic unilateral and/or bilateral peripatellar or retropatellar knee pain; (2) Patellofemoral knee pain with and/or after activity; (3) Inactivity patellofemoral pain and/or stiffness, especially with sitting with knees held in flexed posture; (4) No history of knee surgery; **Physical examination:** (1) No or minimal articular or periarticular effusion or bursitis; (2) No significant joint line tenderness; (3) No intra-articular ligamentous instability; (4) Peripatellar tenderness ± mild inferior patellar pole tenderness; (5) No patellar apprehension; **Other:** (1) Between the age of 18 and 45; (2) Run at least 15 km per week regularly; (3) do not have any other medical conditions; (4) are not participating in any other PFPS treatment; (5) Are heel-toe runners  *c) Interventions: (What will be done to the subjects and for how long?)*  **PILOT TEST:** 10-16 healthy subjects will be recruited internally at the Human Performance Lab to pilot test 8 footwear conditions (±3, ±6, ±9 degree orthotic wedge inserted into the neutral shoe [+=medial. - = lateral; these are standard wedge angles, eg, Fisher et al., 2007]; an off-the shelf adidas ForMotion running shoe (allows slight relative movement at the heel of the shoe between the foot and outsole), and an off-the-shelf adidas shoe with ForMotion restricted [this is the neutral condition]). All shoes are displayed on a separate attachment for this application. Subjects will be asked to run at 4 m/s during 5 motion analysis trials with each shoe condition (i.e. 40 trials total). Order will be randomly assigned. In motion analysis trials, reflective markers are attached to anatomical landmarks of the lower extremity. Subjects run over a force platform while infrared cameras record marker trajectories. The 3D positions of the markers are coupled with the ground reaction forces recorded from the force plate, and through a series of inverse dynamics calculations we are able to indirectly determine forces in the knee joint. Specifically, we are interested in the footwear that can most significantly reduce knee abduction moments. The footwear that shows the best optimization between the mechanical benefit just described, and shoe comfort will be chosen as the intervention condition in the following experiment. The test should take between 1.5-2.5 hours per subject. **PFPS STUDY**: 30 patients with PFPS will be asked to perform 10 motion analysis trials in a laboratory setting. The motion analysis procedure will be the exact same as described in the above pilot test. Of these 10 trials, 5 will be with the intervention shoe determined from the above pilot test, and 5 will be with the neutral running shoe described above. Order will be randomly assigned. One or two more trials/conditions may or may not be added if we find multiple shoes may be of benefit from the pilot test results. The total laboratory setting testing should take 1.5-2.5 hours per subject. Half of the patients will then be given the neutral shoe and the other half will be given one (only one) of the experimental shoes to take home and use when running on a regular basis for six weeks. During this time, subjects will be asked to complete weekly questionnaires which will record their current levels of knee pain and daily running mileage. At the end of the six weeks, subjects may be asked to return to the lab for a secondary motion analysis test in their experimental footwear in the event no difference was found in the first lab test, but a decrease in pain was still noted.  *d) Primary Outcome Variables (Briefly describe what will be measured and how/using what measurement tools)*  Knee joint loading will be calculated through inverse dynamics by coupling ground reaction force data from a Kistler force plate (Kistler AG, Winterthur, Switzerland) with kinematic data recorded by infrared motion analysis cameras (Motion Analysis Corp., Santa Rosa, CA). Specifically, we will look at knee abduction angular impulses (integral of the abduction moment-of-force over time) using the KinTrak program (KinTrak 7.0, University of Calgary, Calgary, AB). Subjective levels of pain will be recorded by 10cm visual analogue scale (VAS).  *e) Limitations (please list briefly any limitations you have identified in the study)*  A large amount of research is being done on PFPS patients presently at the University of Calgary, so subject recruitment may be competitive. To overcome this limitation, we will recruit subjects external from the University of Calgary as well as internally. Volunteers for our study will undergo running motion analysis testing, which may be an attractive experience for some runners, thus improving the attractiveness of this study. Secondly, although subjects will be asked to refrain from participating in any other treatment for their PFPS, such as physiotherapy, throughout the study, there is no way to actually control this. Instead, we will remind patients weekly to avoid these other treatment options, and ask patients to provide an honest account of other treatments they used during the six week study period once the study has completed. This way, we will at least be able to factor this into data analysis. |

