| 8. Recruitment: Number of Local Subjects: 30 Total number of subjects: 30  a) How will you identify local potential subjects?  Patients with PFPS will be recruited from 1) the Sports Medicine Centre at the University of Calgary upon diagnosis with PFPS; 2) by referral from physician offices in the Calgary area upon diagnosis with PFPS; 3) through poster advertisement in various athletic facilities and sports medicine offices around the Calgary area. All subjects recruited will first undergo assessment by a sports medicine physician at the University of Calgary to ensure the subject has PFPS.  b) Who will recruit the local potential subjects?  Physicians in the Calgary area, physicians in the University of Calgary Sports Medicine Clinic and the investigators of this study by poster advertisement and word of mouth.   1. Where will you recruit potential subjects?   See part (a) above.   1. What method(s) will you use to recruit potential subjects?   Posters will be created and supplied to sports medicine physicians in the Calgary area. We will inform these about our study and request that they pass this information along to their patients with PFPS and provide our contact information to them. We will ask that the physicians mention that our study is a possible treatment for PFPS – an appealing thought considering other treatment forms are limited. We will also inform patients that they would be participating in a personalized running analysis – a potentially exciting experience for avid runners. Lastly, we will offer each subject incentives to participate throughout the study such as free running shoes and running apparel.   1. If you recruitment method involves a letter of invitation, poster, advertisement or electronic announcement, have you included a   copy/copies in this application?  ■ Yes, included □ No □ N/A |
| --- |

| SECTION D – BUDGET SUMMARY To comply with regulatory requirements on the University of Calgary, full budget details are essential. YOUR APPLICATION CANNOT PROCEED WITHOUT BUDGETARY DETAILS. If your study is receiving funding from industry or a granting agency, you must attach a detailed budget. Any funding received from any external source is to be identified. |
| --- |

| 1. Human Resources (List all support personnel to be engaged in the study) | | | | | | |
| --- | --- | --- | --- | --- | --- | --- |
| **Position** | **Salary** | | **Benefits** | **Hrs/Wk** | **Total Hrs.** | **Cost** |

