| Graduate student  ([name])  Sport Medicine Physician  ([name]) | $17,500  Volunteer | | N/A | N/A | N/A | $17500  $0  $0  $0  $0 |
|  | | | | | **Subtotal (1)** | **$17500** |
| 2. Service/Procedures (List x-rays ECGs, etc) | | | | | | |
| Service/Procedure | | #Standard Care | | #Research Specific $Cost per item Total | | |
| N/A | | N/A | | N/A $ 0 = $0  X $ = $  X $ = $  X $ = $  X $ = $  X $ = $  X $ = $ | | |
| **Report tests which are usual care but do not include costs for these*  *Tests in your calculations* **Subtotal (2) $0.00** | | | | | | |
| 3. Supplies and Equipment (List all supply and equipment requirements)  Shoes will need to be purchased for up to 30 participants ($100 per shoe x 30 = $3000)  Orthotic wedges MAY need to be purchased if the pre-existing adidas shoe is not used ($20 per wedge x 15 = $300)  Apparel as participation incentives ($20 per t-shirt x 30 = $600)  iPod nano 8GB incentive ($150)  **Subtotal (3) $4050.00** | | | | | | |
| 4.Miscellaneous Items including long term storage and electronic IB preparation  **Subtotal (4) $0.00** | | | | | | |
| 5. Add-on costs: (Please list costs that will not be included in the final total, e.g.. start-up fee)  **COST (Section 1-4): $21550.00** | | | | | | |
| ***Industry Directed Studies Only:*** Overhead (applied to amt rec’d) $N/A | | | | | | |
| REB Review Fee $N/A | | | | | | |
| **TOTAL COST (industry sponsored studies): $N/A** | | | | | | |
| **FUNDING SOURCE(S): Complete sections A and B as applicable** | | | | | | |
| A. **Non-industry Sponsored Funding:**    Canadian Institutes for Health Research – Master’s Award - $17,500 – Received University of Calgary – Faculty of Graduate Studies Scholarship - $3680 – Received | | | | | | |
| **B. Industry Directed Study: N/A** Grant or Contract  Company Name: ____________________________________ Amount per patient $_______________  Contact Person/Phone/Fax/Mail _________________________________________________________  1. Is overhead included in the amount reported above? Yes No Not applicable  2. Will the local investigator or department receive additional funds for participating in this trial? Yes/No | | | | | | |

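### If a wedge is the chosen intervention, the procedures described do not support the claimed patient blinding, and the self-reported pain score is open to expectation bias

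*Protocol*

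**What the plan says.** Protocol item 5 (Basic Study Design) states that "Each patient will be asked to perform trials with a neutral and experimental shoe conditions". Each subject then gets one shoe to take home, with the remark "this will be randomized and blinded for the patients".

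Item 6c (Interventions) gives the detail:
- **Candidates.** The pilot tests eight conditions. Six are a ±3, ±6 or ±9 "degree orthotic wedge inserted into the neutral shoe". The other two are the ForMotion shoe and the neutral shoe, an adidas model with the ForMotion feature restricted.
- **Laboratory exposure.** In the patient study, "5 will be with the intervention shoe determined from the above pilot test, and 5 will be with the neutral running shoe", in random order.
- **Allocation.** "Half of the patients will then be given the neutral shoe and the other half will be given one (only one) of the experimental shoes", for six weeks of regular running.

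Section D, item 3 (Supplies and Equipment) budgets shoes for up to 30 participants and adds: "Orthotic wedges MAY need to be purchased if the pre-existing adidas shoe is not used ($20 per wedge x 15 = $300".

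Item 6d lists pain on a 10 cm visual analogue scale among the primary outcome variables. Item 8 (Recruitment) says of referring physicians: "We will ask that the physicians mention that our study is a possible treatment for PFPS".

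The text at hand describes no masking step, sham insert or check of blinding. Expectation bias is not among the limitations in item 6e.

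**The concern.** The second primary objective concerns a fall in pain, measured by the patient's own rating. Such a rating can move with what the patient believes about the shoe. Blinding is the protection the protocol names against this, so it matters whether the described procedure can deliver it.

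If a wedge is chosen, one arm wears the neutral shoe and the other wears the same shoe with an added angled insert. Each patient has just run five trials in each and then keeps one of the two for six weeks. A shoe with something added is easily taken for the one under test. If the arms then hold different expectations, a difference in pain can appear with no mechanical cause, and randomisation does not remove it.

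A related point concerns interpretation. With no insert in the neutral shoe, the effect of the wedge angle cannot be separated from the effect of having an insert at all. That is partly a choice of comparator, and it is secondary here.

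**Working it through.** **1. Candidates (item 6c).** 6 wedges + 1 ForMotion shoe + 1 neutral shoe = 8, matching the stated eight. Non-neutral candidates: 8 − 1 = 7, of which 6 are wedges in the neutral shoe.

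**2. Budget (Section D).** Supplies: 30 × $100 + 15 × $20 + 30 × $20 + $150 = $3000 + $300 + $600 + $150 = $4050, the stated subtotal. With salary, $17,500 + $4050 = $21,550, the stated cost. The wedge line is therefore inside the total; without it, supplies would be $3750. Wedges per patient: 15 / 30 = 0.5, which equals the half of patients given an experimental shoe. This is consistent with inserts in one arm only. It is not proof, because the line is conditional and does not say who receives them.

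**3. The statements side by side.**

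| Feature | What the protocol describes |
|---|---|
| Claim | Patients blinded to the take-home shoe |
| Exposure before allocation | 5 trials in each shoe |
| Neutral shoe | ForMotion restricted; no insert described |
| Experimental shoe, wedge case | Neutral shoe plus a 3, 6 or 9 degree insert |
| Experimental shoe, other case | ForMotion shoe, no insert |
| Masking or check of blinding | None described |
| Pain outcome | Patient-rated VAS |

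In the wedge case, nothing described makes the two shoes alike to the wearer.

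**4. What a bias could do (illustration).** The documents give no effect size, SD or bias size. Assume no true shoe effect, a two-sided 5% test (sidedness is not stated) and an expectation shift of δ standard deviations.

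- *Between arms, 15 versus 15.* Noncentral t with 28 degrees of freedom and noncentrality δ × √(15/2) = 2.739δ. At δ = 0.5 this is 1.37.
- *Before-after paired test in one arm of 15*, with δ in SDs of the change. Noncentral t with 14 degrees of freedom and noncentrality δ × √15 = 3.873δ. At δ = 0.5 this is 1.94.

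| δ (assumed) | Between arms, P(significant) | Paired, one arm, P(significant) |
|---|---|---|
| 0 | 5.0% | 5.0% |
| 0.2 | 8.3% | 11.2% |
| 0.3 | 12.5% | 19.2% |
| 0.5 | 26.2% | 43.8% |
| 0.8 | 56.2% | 82.1% |

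The first column of results shows the cost of failed blinding, because it reflects a difference in expectation between arms. Item 7 does not state that comparison; it plans a paired t-test of initial against final pain. The second column shows that the paired test does not remove an expectation response. Part of that response would be present even under perfect blinding.

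**The case against.** The strongest reply is that recognising a shoe is not the same as knowing which one is favoured. Running in both lets a patient identify the shoe later received. It does not label that shoe as experimental, and the trial order is random. This is right, and it means the laboratory session alone does not break the blind. In the wedge case, however, one shoe has an added insert and the other has none described, which makes the guess easy.

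Several stronger readings are tempting, and the documents do not support them:
- **That the trial is unblinded whatever shoe is chosen.** If the ForMotion shoe is selected, neither arm has an insert and the neutral shoe may itself be the altered one. Six of seven candidates is a count, not a probability, because selection rests on mechanical benefit and comfort.
- **That the insert is visible.** The protocol does not say how the wedge sits in the shoe. The shoe pictures are in an attachment not at hand.
- **That all patients are told they are getting a possible treatment.** Item 8 is a request to physicians. Other patients come through posters or word of mouth, and the consent form is not available. The phrase also does not say which shoe is the treatment.
- **That the budget proves inserts go to one arm.** The line is conditional, and the pilot wedges have no separate line, so the budget is not a full inventory.

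It is also fair to say that the before-after pain test is weak for reasons unrelated to blinding, and that running in both shoes is needed for the paired loading comparison. Neither point supports the blinding claim.

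**Conclusion.** The point holds conditionally. If a wedge is selected, the procedures described do not support the statement that patients are blinded, and the self-reported pain VAS is exposed to expectation bias. The inverse-dynamics loading outcome is much less affected. This is more than detail left to an analysis plan: blinding is a design feature the protocol asserts, and the makeup of the neutral condition is fixed in the protocol.

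The size of the bias is unknown. Under the assumed 0.2 to 0.5 SD, the false-positive rate of a 15 versus 15 comparison would be 8.3% to 26.2% instead of 5%. Those figures illustrate the exposure; they do not estimate it.

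The conclusion rests on two assumptions: that the neutral shoe carries no insert, since none is described, and that the unseen shoe pictures and consent form contain no masking arrangement. It should be dealt with before the pilot, because the remedy changes the neutral condition.

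**What to change.** If a wedge is selected, fit the neutral shoe with a flat (0 degree) insert of the same material and look, both in the laboratory and for home use. Describe the two to patients neutrally, as two running shoes under comparison. If this is not done, remove the blinding claim from item 5 and add expectation bias for pain to the limitations in item 6e. A week-6 question on which shoe the patient believes they had is a useful option, not a requirement.

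Cost: 15 take-home inserts × $20 = $300 at the budgeted price, taking supplies from $4050 to $4350, plus a few inserts for the laboratory and pilot. The main downside is that the neutral condition must carry the flat insert in the pilot as well, so that the shoe compared there is the shoe used later. If the ForMotion shoe is selected, the insert change does not apply.

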| 2. Does your study involve any of the following (check all that apply)?  ■ Questionnaire □ Interview □ Chart Review □ Database Linkage ■ Bench Science  Has this study received approval from any of the following designated ethics boards in Alberta: CPSA, ACB, U of A, U of L, CREBA?  □ Yes (if Yes, please append letter) ■ No  Has this study received approval from any other REBs  □ Yes (if Yes, please append letter) ■ No |
| 3.Background Rationale:  Running is an activity that nearly 30% of all Canadian adults participate in; however, injuries frequently occur. Most commonly, the runner will suffer from a chronic condition known as patellofemoral pain syndrome (PFPS), which is characterized by general pain in the anterior knee joint. In fact, over one quarter of all running injuries are PFPS in nature and this amounts to over one million Canadians affected annually. Although the exact biological nature of PFPS is not known, it has been shown through a prospective and retrospective biomechanical evaluation of runners that increased knee abduction moments-of-force may be implicated in the development and continuance of PFPS. Therefore, reducing these moments-of-force may be a possible treatment for PFPS patients.  Reducing knee joint loading can be accomplished through footwear intervention. This has been done successfully for healthy subjects and subjects with knee osteoarthritis. For osteoarthritic patients, not only was the knee joint loading reduced, but subjective levels of pain were decreased over time. The effects of these footwear interventions on patients with PFPS are currently not known. |
| 4.Hypothesis/Research Question/Objectives:  Primary Objectives:   1. Determine if a footwear intervention can reduce knee joint loading for runners with PFPS. 2. Determine if this decrease in knee joint loading corresponds to a decrease in subjective levels of pain over time.   Hypotheses:   1. We expect that footwear can decrease knee joint loading for PFPS subjects since this has been done for healthy subjects and patients with knee osteoarthritis. 2. If knee joint loading can be reduced, we expect a decrease in subjective levels of pain over a period of six weeks. |

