| --- |
| 7.Statistical Considerations in the study design:   1. *What is your sample size and how do you justify it? (Provide details of sample size calculation)*   Our sample size will be 30 subjects. No pilot test data or data from other researchers’ studies exist in regards to PFPS patient footwear interventions focusing on knee joint loading, thus power analyses cannot be properly performed at this time. However, in most biomechanical studies, a sample size between 10-16 subjects can achieve over 80% power. This is because many biomechanics studies, including the one proposed in this application, employ a paired-samples statistical design, thereby reducing within subject error. Therefore, our planned sample size of 30 should be more than sufficient. Once testing begins, and results from 6-8 subjects are known, full power analyses will be conducted to ensure over 80% power will be reached through 30 subjects. Sample size will be adjusted accordingly.   1. *Data Analysis (Which method of analysis will you use?)*   As mentioned above, the study will use a paired-samples design. Each subject’s motion analysis experimental condition will be compared against their own neutral condition. Thus a paired-samples t-test (a=0.05) will be used here. In the second part of the study, where subjects are asked to run on their own for six weeks, their initial pain score data will be used as a baseline for comparison to their final pain score. Thus, a paired-samples t-test (a=0.05) will be used here as well. |

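### The two planned paired t-tests cannot answer primary objective 2: neither measures an association between loading and pain, and the pain test makes no use of the randomised neutral-shoe group

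*Protocol*

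**What the plan says.** **Objective.** Protocol item 4 gives primary objective 2 as "Determine if this decrease in knee joint loading corresponds to a decrease in subjective levels of pain over time". Item 5 states the expected conclusion more strongly: "we will be able to determine if a decrease in knee joint loading is correlated with a decrease in knee pain".

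**Design.** Under items 5 and 6c, every patient runs five laboratory trials in the intervention shoe and five in the neutral shoe. Patients are then randomised, blinded, so that half take home the neutral shoe and half an experimental shoe for six weeks. Knee pain is reported weekly.

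**Analysis.** Item 7 asks directly which method will be used and gives two. For loading, "Each subject’s motion analysis experimental condition will be compared against their own neutral condition" by a paired t-test. For the six-week phase, "their initial pain score data will be used as a baseline for comparison to their final pain score", followed by "Thus, a paired-samples t-test (a=0.05) will be used here as well". The protocol names no correlation, regression or between-shoe comparison. Item 6e mentions taking other treatments into account in the analysis, which is a separate matter.

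**Sample size.** "Our sample size will be 30 subjects". The support is that "in most biomechanical studies, a sample size between 10-16 subjects can achieve over 80% power", an argument resting on the paired design.

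**The concern.** A paired t-test concerns the mean of one set of differences. The loading test asks whether the mean laboratory difference between shoes is zero. The pain test asks whether the mean change over six weeks is zero. Neither looks at how the two changes vary together, which is what a correlation is.

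The pain test has a second gap. It compares patients with their own baseline and makes no contrast between the randomised shoes. Item 7 does not say whether the test pools the shoes or is run within each, but in neither case is one shoe compared with the other. A fall in pain could then reflect natural course or regression to the mean, since patients enter with symptomatic knees.

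If the plan is followed as written, the study would infer a link between load and pain from two mean changes that happen to coincide. That inference bears on a primary objective.

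**Working it through.** **1. The plan's own figure.** N = 30 cannot be reproduced, because no effect size or SD is given ("thus power analyses cannot be properly performed at this time"). Solving the noncentral t for a paired test (two-sided alpha 0.05, 80% power) gives the standardised mean change that each sample size implies: 1.00 at n = 10, 0.75 at n = 16 and 0.53 at n = 30. These concern one mean change. They say nothing about an association or a between-shoe difference.

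**2. Do two significant t-tests indicate association?** Inputs, all assumed: loading change and pain change bivariate normal, each with mean 0.8 SD, true correlation rho varied, 20,000 simulated trials per setting. Proportion of trials significant:

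| n | rho | Loading t-test | Pain t-test | Both | Pearson test |
|---|---|---|---|---|---|
| 30 | -0.8 | 0.988 | 0.988 | 0.976 | 1.000 |
| 30 | 0 | 0.988 | 0.989 | 0.976 | 0.048 |
| 30 | 0.5 | 0.988 | 0.989 | 0.978 | 0.830 |
| 30 | 0.8 | 0.989 | 0.989 | 0.982 | 1.000 |
| 15 | -0.8 | 0.820 | 0.824 | 0.647 | 0.975 |
| 15 | 0 | 0.821 | 0.821 | 0.676 | 0.050 |
| 15 | 0.5 | 0.827 | 0.823 | 0.718 | 0.499 |
| 15 | 0.8 | 0.824 | 0.825 | 0.756 | 0.980 |

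Each t-test's rejection rate does not depend on rho. At n = 30 the joint result is practically the same for a strong negative, a zero and a strong positive correlation. At n = 15 it moves only from 65% to 76%.

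**3. What a between-shoe pain comparison can detect.** With 15 per arm, the normal approximation is (1.96 + 0.84) × sqrt(2/15) = 2.80 × 0.365 = 1.02 SD. The noncentral t with 28 degrees of freedom gives 1.06 SD. Baseline adjustment reduces this by a factor of about sqrt(1 − c²), where c is the baseline-to-final correlation of VAS; the protocol does not give c.

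**4. What an association analysis can detect** (Fisher z, two-sided alpha 0.05, 80% power): detectable r = tanh(2.80 / sqrt(n − 3)).

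- Experimental-shoe arm, n = 15: tanh(2.80 / sqrt(12)) = tanh(0.808) = 0.67.
- All patients, n = 30: tanh(2.80 / sqrt(27)) = tanh(0.539) = 0.49.
- 95% CI at n = 15 if the observed r is 0: ± tanh(1.96 / sqrt(12)) = ± tanh(0.566) = ± 0.51.

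The n = 30 figure is for reference only. Neutral-shoe patients do not wear the load-reducing shoe at home, so their laboratory reduction is not an exposure during the six weeks. If their change is instead coded as zero, the correlation largely reflects the shoe contrast.

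**5. An interaction of arm and laboratory reduction.** Comparing two independent correlations with 15 per arm and no association in the neutral arm, the standard error on the z scale is sqrt(1/12 + 1/12) = 0.408. The detectable r in the experimental arm is tanh(2.80 × 0.408) = tanh(1.143) = 0.82. This is a guide, since the regression interaction also depends on the residual variances in the two arms.

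**The case against.** The strongest objection is that objective 2 need not be a patient-level claim. It asks whether the decreases correspond, and its hypothesis in item 4 is conditional and reads at group level: if loading can be reduced, pain is expected to fall. Item 6c likewise treats the two results as group-level steps, allowing a repeat laboratory test if pain falls without a loading difference. The patient-level reading rests mainly on the word *correlated* in a brief design summary.

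This stands as a limit on the claim. A reader might infer that objective 2 is unambiguously a within-patient association; the documents do not settle that. It does not rescue the analysis, because the group-level reading needs a comparison of pain between the randomised shoes, and the pain test makes none.

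A reader might also infer that an interaction of arm and laboratory reduction should be the deciding test. That is not supported: it is weaker than a one-arm correlation, and it would displace the randomised contrast as the main answer. If the pilot leads to several experimental shoes, as item 6c permits, the reduction for neutral-arm patients is also not uniquely defined.

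Finally, a statistical analysis plan that is not shown could add an association analysis. That carries little weight here, because item 7 answers the question of method outright and the method it fixes does not match the objective.

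**Conclusion.** The concern holds: the analysis fixed in item 7 cannot answer primary objective 2 on either reading, and the conclusion promised in item 5 would be unsupported. With 30 patients and assumed mean changes of 0.8 SD, both tests come out significant in about 98% of trials when the changes are unrelated. An association analysis in the arm that wears the experimental shoe would be informative only for strong links (|r| of about 0.67 or more), so a promise to determine the correlation is too strong even once an analysis is added.

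The finding does not touch objective 1; the within-patient loading comparison suits that question. The figures assume two-sided testing at 0.05, which the protocol does not state, and 15 patients per arm. Item 7 allows the sample size to be adjusted after the first 6-8 subjects, which would change the detectable values but not the mismatch.

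**What to change.** 1. In item 7, replace the paired t-test on pain, as the test for objective 2, with a between-shoe comparison of final VAS adjusted for baseline VAS (ANCOVA). The power analysis already planned after 6-8 subjects should address this comparison.
2. Add an exploratory estimate, with 95% CI, of the association between each patient's laboratory reduction in knee abduction angular impulse (neutral minus experimental) and pain change within the experimental-shoe arm. State its limited precision.
3. An interaction of arm and laboratory reduction may be reported as supportive, with a statement that it is weaker (80% power only at about r = 0.82 in the experimental arm if there is none in the neutral arm). If more than one experimental shoe is tested, say which defines the reduction for neutral-arm patients.
4. In item 5, replace the promise to determine the correlation with a statement that the association will be estimated with a 95% CI.

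**Cost.** Analysis wording and a little more analysis; loading in both shoes and pain scores are already planned for every patient. The downside is a weaker stated claim, and a between-shoe test that, at 15 per arm, can reliably detect only a large difference.
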